#### 7.4.1.1 Management of proteinuria

If a patient has a change of two plus (++) from baseline on two consecutive urine protein dipstick measurements, please measure urine protein creatinine ratio or collect a 24-hour urine for total protein. A urine protein/creatinine ratio of 0.15 (urine protein and urine creatinine expressed in mg/dL) approximates a 24-hour urine protein of 150 mg/24 hours or 0.15g/24 hours, which is the upper limit of normal. If 24 hour proteinuria or UPC ratio is classified as CTCAE grade 3 or more please follow guidance in [Section 7.4.1](#).

**Table 6.** Approximation of the urinary protein / creatinine ratio to the CTC grading of proteinuria (from CTCAE v4.03:

| Assessment (for Proteinuria)       | CTC Grade 1   | CTC Grade 2         | CTC Grade 3   | CTC Grade 4 | CTC Grade 5 |
|------------------------------------|---------------|---------------------|---------------|-------------|-------------|
| Dipstick                           | 1+            | 2+                  |               |             |             |
| 24-hour urine protein              | <1.0 g/24 hrs | >1.0 – 3.4 g/24 hrs | >3.5 g/24 hrs |             |             |
| Urinary protein / creatinine ratio |               | 0.5-1.9             | >1.9          |             |             |

Note: For UPC Ratio, obtain first morning void samples if possible and obtain at least 2 baseline samples. Urine protein and urine creatinine expressed in mg/dL.

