### 5.1.2 Exclusion Criteria

Any of the following is regarded as a criterion for exclusion from the study:

- Patients on enzyme-inducing anti-epileptic drugs (see [section 7.5](#)) within 2 weeks prior to study enrolment. Note: Patients are eligible if they switched to non-enzyme inducing agents and discontinued enzyme-inducing agents for more than or equal to 2 weeks prior to randomisation
- Inadequate bone marrow reserve as demonstrated by an absolute neutrophil count  $\leq 1.5 \times 10^9$  /L or platelet count  $\leq 100 \times 10^9$  /L or requiring regular blood transfusions to maintain haemoglobin  $>9\text{g/dL}$
- Serum bilirubin  $\geq 1.5 \times \text{ULRR}$  (except for patients with known documented cases of Gilbert's Syndrome)
- ALT or AST  $\geq 5 \times \text{ULRR}$
- Serum creatinine  $>1.5 \times \text{ULRR}$  or a creatinine clearance of  $\leq 50\text{mL/min}$  calculated by Cockcroft-Gault

- Greater than +1 proteinuria on two consecutive dipsticks taken no less than 1 week apart unless urinary protein <1.5g in a 24 hr period or UPC (Urine Protein: Creatinine) ratio <1.5
- History of significant gastrointestinal impairment, as judged by the investigator, that would significantly affect the absorption of cediranib or gefitinib, including the ability to swallow the tablet whole
- Patients with a history of poorly controlled hypertension with resting blood pressure >150/100mmHg in the presence or absence of a stable regimen of anti-hypertensive therapy, or patients who are requiring maximal doses of calcium channel blockers to stabilise blood pressure
- Any evidence of severe or uncontrolled diseases (e.g. unstable or uncompensated respiratory, cardiac, hepatic or renal disease)
- Unresolved toxicity >CTC AE grade 1 from previous anti-cancer therapy (including radiotherapy) except alopecia (if applicable)
- Mean QTc with Bazetts correction >470msec in screening ECG or history of familial, long QT syndrome (see Appendix 7)
- Cardiac ventricular arrhythmias requiring anti-arrhythmic therapy
- Significant haemorrhage (>30mL bleeding/episode in previous 3 months) or haemoptysis (>5mL fresh blood in previous 4 weeks)
- Recent (<14 days) major surgery or brain biopsy. Recent craniotomy (<28 days) prior to first dose, or a surgical incision that is not fully healed
- Pregnant or breast-feeding women or women of childbearing potential with a positive pregnancy test prior to receiving study medication (see [section 5.1.3](#))

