## 5.2 Pre-randomisation evaluation

Patients must give written informed consent before any trial specific screening investigations may be carried out. The following assessments or procedures are required to evaluate the suitability of patients prior to entry:

- Confirmation (histological/cytological) that patient has glioblastoma (WHO grade IV)
- Within 7 days prior to randomisation:
  - Brain Tumour assessment: MRI scan of the tumour region, where the tumour is the largest. –See [section 7.7](#) (Imaging) for the list of required scans.
  - Demographic details including date of birth, sex, and race
  - Relevant medical and surgical history, including previous hypertension, ongoing medication and documentation of baseline symptoms
  - Physical examination: height and weight, vital signs (including pulse, lying and 5 min standing blood pressure, respiratory rate and temperature)
  - ECOG performance status
  - Karnofsky performance status

- Mini-mental status exam
- Neurological examination
- Full blood count (FBC)
- Serum biochemistry: sodium, potassium, urea, creatinine, phosphate, total protein, albumin, globulin, adjusted calcium, total bilirubin, alkaline phosphatase, AST and/or ALT, LDH and gamma-GT.
- Clotting function tests (PT/APTT)
- Thyroid function tests
- Urinalysis: dip-stick test for protein. If a patient has two consecutive urine protein measurements of greater than one plus (+) taken no less than 1 week apart then measure urine protein:creatinine ratio or collect a 24-hour urine for total protein. A urine protein/creatinine ratio of 0.15 (urine protein and urine creatinine expressed in mg/dl) approximates a 24-hour urine protein of 150mg/24 hours or 0.15 g/24 hours, which is the upper limit of normal.
- Pregnancy test (if applicable – i.e females of child bearing potential (see [section 5.1.3](#)))
- ECG with estimation of QTc interval (see Appendix 7)

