### 7.4.1 Management of toxicity attributable to cediranib

Dose interruptions should be used as the first approach to managing toxicity and dose reduction may be considered.

The events for which de-escalation of the cediranib dose is recommended include, with the EXCEPTION of hypertension:

- CTCAE grade 3 or higher toxicities of duration >3 days that are considered to be related to study treatment that are not responding to maximal supportive care within 48 hours, at the discretion of the investigator.

With the EXCEPTION of

- proteinuria (see [Section 7.4.1.1](#)),
- hypothyroidism (see [Section 7.4.1.2](#))
- hypertension (see [Section 7.4.1.4](#)), and
- reversible posterior leucoencephalopathy syndrome (RPLS) (see [Section 7.4.1.7](#)),

the following management plan should be followed for management of toxicity attributable to cediranib:

Dose interruptions should be used as the first approach to managing toxicity. For CTC Grade 3 or more, dosing with cediranib should be interrupted. Cediranib dosing may be withheld for up to 14 days (21 days in consultation with the CI) for management of toxicity. If a longer interruption is required due to unresolved toxicity, cediranib should be discontinued.

- If the symptoms promptly resolve to grade 1 or below with supportive care, consideration should be given to continuing the same dose of cediranib along with appropriate continuing supportive care
- If the symptoms of the toxicity are considered related to cediranib and do not resolve to grade 1 or below with maximum supportive care and following a dose interruption of up to 14 days (21 days in consultation with the CI), the next dose level of cediranib below that being dosed should be instituted
- If symptoms do not resolve, and it is considered medically appropriate, investigators may choose to permanently discontinue cediranib

For patients who have multiple low grade adverse events (for example, diarrhoea, weight loss, dehydration and fatigue) short dose interruptions (ie, 2 - 5 days) of cediranib tablets may help. Treatment can be restarted on resolution at the same dose.

Two dose reductions for the cediranib treatment will be permitted during the study. No re-escalation of dose is permitted.

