### c) Urinalysis tests

Urinalysis- if a patient has two consecutive one plus (+) urine proteinuria dipsticks measurements at baseline, please measure urine protein/creatinine ratio (UPC) or collect 24 hours urine for total protein. If the patient has a change of two plus (++) or greater from baseline on two consecutive proteinuria dipsticks, please measure urine protein/creatinine ratio or collect 24 hours urine for total protein. If 24 hours protein or UPC Ratio is classified as CTCAE grade 3 please refer to and follow guidance in [section 7.4.1.1](#), management of proteinuria.

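### The on-treatment trigger for measuring urine protein misses a confirmed rise from 2+ to 3+ in patients admitted with proteinuria already above 1+

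*Protocol*

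**What the plan says.** **Entry.** Protocol 5.1.2 excludes patients above 1+ on two dipsticks at least a week apart, with an exception: "unless urinary protein <1.5g in a 24 hr period or UPC (Urine Protein: Creatinine) ratio <1.5". Section 5.2 requires a UPC or 24-hour collection before randomisation after "two consecutive urine protein measurements of greater than one plus (+) taken no less than 1 week apart". Section 8.2 c sets a lower threshold at baseline, asking for the same test "if a patient has two consecutive one plus (+) urine proteinuria dipsticks measurements at baseline". Both entry rules use an absolute dipstick reading.

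**On treatment.** Section 7.4.1.1 asks for a UPC or 24-hour collection under this condition: "If a patient has a change of two plus (++) from baseline on two consecutive urine protein dipstick measurements". Section 8.2 c has the same rule: "If the patient has a change of two plus (++) or greater from baseline on two consecutive proteinuria dipsticks". Both measure change from the patient's own baseline, and neither adds an absolute threshold.

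**Action.** Section 7.4.1.1 continues: "If 24 hour proteinuria or UPC ratio is classified as CTCAE grade 3 or more please follow guidance in" section 7.4.1. That section says: "For CTC Grade 3 or more, dosing with cediranib should be interrupted". In Table 6 the dipstick row ends at 2+ (grade 2). Grade 3 is UPC above 1.9 or more than 3.5 g/24 h, and its dipstick cell is empty. The note under the table says to "obtain first morning void samples if possible and obtain at least 2 baseline samples".

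**Schedule.** Section 8.1 places urinalysis at screening, baseline, weeks 3 and 6, each later 6-weekly cycle start, and discontinuation. It schedules no on-treatment UPC.

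**The concern.** The entry exception knowingly admits some patients at 2+ or more. The on-treatment rule then asks for a two-step rise from wherever each patient began, so the higher the starting reading, the higher the reading needed before anyone must measure protein. The patients who enter with proteinuria are thus the ones for whom the rule is least sensitive.

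This matters because the dipstick alone cannot establish grade 3, and only a quantified grade 3 result leads to the interruption step. If the rule is followed to the letter, grade 3 proteinuria could go unmeasured while cediranib continues. The toxicity is an expected one: sections 2.3.1 and 2.3.2 list proteinuria among the common side effects of both drugs. An event that is never measured could also be absent from the count of treatment-related grade 3 or higher events that guides safety review in 16.5.

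**Working it through.** The protocol gives no figure to reproduce. The check sets the rules side by side and uses simple arithmetic.

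**Inputs.** Trigger: two dipstick steps above baseline, on two consecutive dipsticks (7.4.1.1, 8.2 c). Entry limits: UPC 1.5, 24-hour protein 1.5 g (5.1.2). Grade 2 lower edges: UPC 0.5, 24-hour protein 1.0 g. Grade 3 limits: UPC 1.9, 24-hour protein 3.5 g (Table 6). Assumptions: readings move in whole plus steps, and the top of the scale is either 3+ or 4+, because the protocol names neither.

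**Step 1: reading that forces a measurement.** Reading needed twice = baseline + 2 steps.

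| Baseline | Needed twice | Scale ending at 3+ | Scale ending at 4+ |
|---|---|---|---|
| negative | 2+ | reachable | reachable |
| 1+ | 3+ | top reading | reachable |
| 2+ | 4+ | not reachable | top reading |
| 3+ | 5+ | not reachable | not reachable |

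One result does not depend on the scale: from 2+, a confirmed 3+ is a one-step rise, and one step is less than two. It never triggers the test.

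**Step 2: can the dipstick stand in for the test?** No. Table 6 gives no dipstick reading for grade 3, so a patient at 3+ cannot be placed in or out of grade 3 without a UPC or 24-hour result.

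**Step 3: distance from entry to grade 3.** Ratio = grade 3 limit / starting value.

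- UPC at the entry limit: 1.9 / 1.5 = 1.27-fold.
- UPC at the lower edge of grade 2: 1.9 / 0.5 = 3.8-fold.
- 24-hour protein at the entry limit: 3.5 / 1.5 = 2.33-fold.
- 24-hour protein at the lower edge of grade 2: 3.5 / 1.0 = 3.5-fold.

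Patients who start below those lower edges have more room still.

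**Step 4: entry against treatment.** A confirmed 3+ at screening must be quantified under 5.2. The same confirmed 3+ on treatment need not be, if the patient started at 2+.

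**Step 5: the link to interruption.** Section 7.4.1 lists proteinuria among its exceptions and sends the reader to 7.4.1.1, which sends a grade 3 result back to 7.4.1. The references are circular, and the natural reading is that cediranib is interrupted at grade 3.

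**The case against.** The strongest reply is that this is a design choice with a purpose. A baseline-relative rule looks for treatment-emergent change, whereas an absolute threshold suits eligibility; the two tasks differ, and these patients have already been quantified at screening. Section 7.4 presents its content as recommended general guidance, so the trigger is a minimum and an investigator may test sooner. That stands: the entry and treatment rules do not contradict each other. It does not remove the gap, because the written minimum still leaves out the patients for whom a small dipstick change may matter most.

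Other safeguards exist:

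- A worsened pre-existing condition is an adverse event (10.2.1) and is graded by CTCAE where possible (10.2.1.3). With no dipstick grade above 2+, grading a worsening to 3+ points towards the quantified test.
- Clinical chemistry is taken at the same scheduled visits as urinalysis.
- Section 7.4.4 recommends interrupting both drugs at creatinine clearance below 30 mL/min.
- Section 13.1.1 stops both drugs for nephrotic syndrome.
- The baseline UPC samples in the Table 6 note give a comparator.

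These limit the consequence, but each is indirect, late or confined to baseline. None orders the on-treatment test.

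The affected group is also narrow. Section 5.1.2 separately excludes raised creatinine, creatinine clearance of 50 mL/min or less, and severe or uncontrolled renal disease. Nothing shows that any patient at 3+ with UPC below 1.5 would be enrolled.

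**Conclusion.** The point holds as a minor safety weakness. For a patient who enters at 2+, the protocol never requires quantification on a confirmed rise to 3+, although only quantification can identify the grade at which cediranib is interrupted. This follows from the text whatever the dipstick scale.

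Three stronger readings are tempting and are not supported:

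- A reader might infer that the trigger can never fire from 2+. That is true only on a scale ending at 3+; on one ending at 4+ it fires at the top reading. The protocol does not say which is used.
- A reader might take the 1.27-fold figure as typical of these patients. It applies only at the exact UPC entry limit; the other starting points worked above give 2.33-fold to 3.8-fold. None of these ratios is a probability of reaching grade 3 undetected, and the document offers no basis for one.
- A reader might infer harm to the trial's conclusions. The primary analysis is unaffected, and any undercount in the 16.5 safety tally cannot be sized.

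The number of patients entering at 2+ or more is not given. That it is small, out of a target of 112, is a judgement.

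**What to change.** In 7.4.1.1 and 8.2 c, add that patients whose baseline dipstick is 2+ or more have a spot UPC at each scheduled urinalysis, or on any dipstick rise from baseline. Keep the two-step rule for all other patients. No change to the visit schedule is needed, since the ratio can be run on urine already being tested.

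The cost is a wording change and a few extra ratios in a group that is probably small. The downside is that slightly more proteinuria may be recorded, with possibly a few more cediranib interruptions.

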### Stopping criteria

A treatment-related grade  $\geq 3$  toxicity rate of 30% in any treatment group along with any other clinical data agreed by the Independent data Monitoring Committee would be used as a guide to consider stopping the trial. As soon as 17 patients out of 56 (30%) in one of either arm suffer a grade  $\geq 3$  treatment-related event, this would prompt us to review the safety data more frequently. If at least 24 patients (43%) have a grade  $\geq 3$  treatment-related event, this would require the IDMC to consider stopping the trial early for safety reasons. The IDMC will be able to compare the toxicity rates between the treatment arms. All safety data will be reviewed regularly. This will be at least every 6 months by members of the TMG in a blinded fashion and at every IDMC meeting. Should stopping be considered due to safety reasons, the IDMC will meet at the earliest convenient time.

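### On the protocol's approximate ratio-to-24-hour equivalence, the two rows of Table 6 grade the same proteinuria differently, so grade 3 can depend on which permitted test was done

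*Protocol*

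**What the plan says.** Section 7.4.1.1 applies after a rise of two plus from baseline on two consecutive dipsticks. The site is then told: "please measure urine protein creatinine ratio or collect a 24-hour urine for total protein". No order of preference is given. The same paragraph relates the two tests: "A urine protein/creatinine ratio of 0.15 (urine protein and urine creatinine expressed in mg/dL) approximates a 24-hour urine protein of 150 mg/24 hours". Section 5.2 repeats that statement for screening. The exclusion criteria in section 5.1.2 set alternative limits at a higher level: "unless urinary protein <1.5g in a 24 hr period or UPC (Urine Protein: Creatinine) ratio <1.5".

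Table 6 then grades each test on its own row:

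- 24-hour protein: grade 1 below 1.0 g, grade 2 ">1.0 – 3.4 g/24 hrs", grade 3 above 3.5 g.
- Ratio: grade 2 from 0.5 to 1.9, grade 3 above 1.9.
- Dipstick: 1+ is grade 1 and 2+ is grade 2, with nothing higher.

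The grade has consequences. Section 7.4.1.1 says "If 24 hour proteinuria or UPC ratio is classified as CTCAE grade 3 or more please follow guidance in" section 7.4.1, and that section says "For CTC Grade 3 or more, dosing with cediranib should be interrupted". At trial level, the stopping criteria in section 16.5 count patients with treatment-related events of grade 3 or above: "As soon as 17 patients out of 56 (30%) in one of either arm suffer a grade" 3 or higher event of that kind, safety data are reviewed more often. At 24 patients (43%) the IDMC must consider stopping.

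**The concern.** Table 6 is there to let either test yield a CTC grade. If the two tests are roughly interchangeable number for number, as the text above the table suggests, one level of protein excretion should receive one grade whichever test the site orders. The printed cut-offs do not do that: grade 3 begins above 1.9 on one row and above 3.5 on the other.

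Because the dipstick row stops at grade 2, every grade 3 proteinuria has to come from one of these two rows. A site that habitually sends a spot ratio and a site that habitually collects urine could then grade similar patients differently. They would handle cediranib differently under section 7.4.1 and contribute differently to the count of grade 3 events that the IDMC sees. Proteinuria is listed as a side effect of both cediranib (section 2.3.1) and gefitinib (section 2.3.2), so the situation is a foreseeable one.

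**Working it through.** **Inputs.** The equivalence in section 7.4.1.1 (ratio 0.15, 0.15 g/24 h); the paired limits in section 5.1.2 (1.5 g, ratio 1.5); the cut-offs in Table 6.

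**Step 1: the conversion the protocol implies.**

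- Section 7.4.1.1: 0.15 g ÷ 0.15 = 1.0 g/24 h per unit of ratio.
- Section 5.1.2: 1.5 g ÷ 1.5 = 1.0 g/24 h per unit of ratio.

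The two places agree.

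**Step 2: grade each level on both rows, using 1.0 g per unit.**

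| Ratio, and matching g/24 h | Grade by ratio row | Grade by 24-hour row |
|---|---|---|
| 0.5 to below 1.0 | 2 | 1 |
| exactly 1.0 | 2 | none assigned |
| above 1.0 to 1.9 | 2 | 2 |
| above 1.9 to 3.4 | 3 | 2 |
| above 3.4 to 3.5 | 3 | none assigned |
| above 3.5 | 3 | 3 |

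In steps of 0.1, all 15 values from 2.0 to 3.4 disagree. For example, a ratio of 2.5 is grade 3 and 2.5 g/24 h is grade 2. Lower down, a ratio of 0.7 is grade 2 and 0.7 g/24 h is grade 1.

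**Step 3: size of the mismatch.** The ratio cut-off for grade 3 is 1.9 ÷ 3.5 = 0.54 of the 24-hour cut-off. For a ratio of 1.9 to line up with the 24-hour boundary, the conversion would need to be 3.4 ÷ 1.9 = 1.79 to 3.5 ÷ 1.9 = 1.84 g per unit. For 0.5 to line up with 1.0 g it would need to be 1.0 ÷ 0.5 = 2.0. So a factor of about 1.8 to 2.0 would bring the rows close to each other, but the protocol states 1.0.

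**Step 4: gaps that need no conversion.** The 24-hour row reads below 1.0, above 1.0 to 3.4, and above 3.5. Exactly 1.0 g, and anything above 3.4 up to and including 3.5 g, has no grade as printed.

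**Step 5: the triggers.** 17/56 = 30.4% and 24/56 = 42.9%, matching the protocol's rounded figures. The protocol gives no expected rate of proteinuria, so the effect on these counts cannot be calculated.

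**The case against.** The strongest reply is that the protocol does not assert equality. The verb is *approximates*, the table's own title calls it an approximation, and the relation is stated only at 0.15, the upper limit of normal. The disputed upper range is 13 to 23 times higher (2.0 ÷ 0.15 = 13.3; 3.4 ÷ 0.15 = 22.7). The 1.5 pairing in the exclusion criteria sets two alternative limits rather than a conversion, and at 1.5 both rows of Table 6 give grade 2. This stands as a limit on the claim. A reader might infer a flat contradiction in which the statements cannot all be true, and the text does not go that far. What the reply does not explain is a grade 3 cut-off on one row at 54% of the other. Nor does it remove the lower disagreement, which lies between the two levels, 0.15 and 1.5, at which the protocol pairs the tests.

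Table 6 also attributes its grading to CTCAE v4.03. Whether both rows come from that source cannot be checked here. If they do, the mismatch with the protocol's own equivalence remains, but the remedy may lie in the equivalence statement rather than in the rows.

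Three further points on the other side hold:

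- If both tests are done, the wording already makes grade 3 on either one lead to section 7.4.1. The problem arises when only one is done.
- Neither test is prompted on treatment until the dipstick change has been seen twice, which narrows the group.
- The lower disagreement (grade 1 versus 2) reaches neither the grade 3 rule nor the stopping count. At most it could bear on recovery to grade 1, which section 7.4.1 uses when deciding how to resume.

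**Conclusion.** The point holds in a limited form. On the protocol's approximate one-to-one relation, extended above 1.5, the two rows of Table 6 give different grades for ratios above 1.9 up to 3.4 (grade 3 versus 2) and from 0.5 to just under 1.0 (grade 2 versus 1). The gaps in the 24-hour row stand without any conversion. Where one test is done, the choice of test can decide whether grade 3 management applies and whether a treatment-related event is counted toward the 17- and 24-patient triggers.

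Two stronger readings are not supported:

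- That every patient between 1.9 and 3.5 g is graded 3 by one test and 2 by the other. A ratio of exactly 1.9 is grade 2, and 24-hour values above 3.4 to 3.5 g have no grade.
- That the comparison of arms or the stopping guide is distorted. Treatment is double-blind, test choice is local, the triggers count any treatment-related grade 3 or higher event and serve as a guide, and the definition of progression does not use proteinuria grade.

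The number of patients affected is unknown.

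**What to change.** The sponsor should:

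- reconcile the ratio and 24-hour rows of Table 6 with each other and with the equivalence stated in sections 7.4.1.1 and 5.2;
- if the two rows are meant to stand as they are, say at what level the stated equivalence is intended to apply;
- close the gaps in the 24-hour row at 1.0 g and between 3.4 and 3.5 g;
- record on the CRF which test produced the grade, so that the safety tables and IDMC reports can be read accordingly.

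Which cut-offs apply is for the sponsor to settle; this review takes no view. The cost is a correction to one table and its accompanying sentence, plus one CRF field. No additional tests or visits are needed.
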